## Study Objectives

The objective of this study is to determine whether the device differences observed in *in vitro* measurements have a clinically meaningful impact on treatment success in the emergency setting (*in vivo*). The differences in delivered drug dose between the Babyhaler (BH) and OptiChamber Diamond (OD) devices are substantial (Figure 3). These differences are assumed to affect the bronchodilator treatment response, particularly in young children with moderate to severe respiratory distress. In this patient group, breathing is often highly variable, shallow, and rapid—factors that make the administration of inhaled medications especially challenging.

The study will assess whether there is a difference between the Babyhaler and OptiChamber Diamond in the treatment of acute respiratory distress in children in terms of:

1. Symptom relief (Tables 2 and 3)
2. Probability of hospitalization
3. Symptom recurrence (return visits within 48 hours of discharge)
4. Treatment acceptance (which device children tolerate better; Table 4)
5. Adverse effects

**Table 2.** Respiratory Distress Assessment Instrument (RDAI) scoring [11]

|                    | Points |      |          |        |     | Max. score |
|--------------------|--------|------|----------|--------|-----|------------|
|                    | 0      | 1    | 2        | 3      | 4   |            |
| Wheezing    |        |      |          |        |     |            |
| Expiration         | none   | End  | ½        | ¾      | all | 4          |
| Inspiration        | none   | Part | All      | –      | –   | 2          |
| Lung fields        | none   | Part | All      | –      | –   | 2          |
| Retractions |        |      |          |        |     |            |
| Supraclavicular    | none   | Mild | Moderate | Marked | –   | 3          |
| Intercostal        | none   | Mild | Moderate | Marked | –   | 3          |
| Subcostal          | none   | Mild | Moderate | Marked | –   | 3          |

The maximum score for wheezing is 8, and for the use of accessory muscles 9.  
Diminished breath sounds correspond to 8 points for wheezing.

**Table 3.** Clinical variables monitored and differences between groups

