| RDAI-scores
<del>SaO2</del> | SaO2 (Amended in 13.1.2025. Decision made to have only one primary outcome that was the base of the sample size calculation. SaO2 was moved from Main outcomes to Secondary outcomes)
Change in respiratory rate (difference before and after medication)
Heart rate (difference before and after medication)
<del>Need for oral prednisolone</del> (Amended in 25.2.2021. The proportion of children receiving oral corticosteroids will be reported as baseline characteristic instead of outcome because they were often given before and/or during the intervention)
Number (proportion) of patients admitted to the hospital
Parents' assessment of treatment success (Table 4)
Healthcare personnel's assessment of treatment success (Table 4)
Proportion of patients requiring a fourth dose of medication
<del>Number of return visits</del> (Amended in 25.2.2021. Outcome removed because it is not feasible to collect the data reliably in all the centers) |

**Table 4.** Assessment of treatment adherence and perceived effectiveness of inhalation therapy using a structured scoring system

|                                  | Points |   |   |   |   |   |
|----------------------------------|--------|---|---|---|---|---|
|                                  | 0      | 1 | 2 | 3 | 4 | 5 |
| Evaluated by the nurse           | 0      | 1 | 2 | 3 | 4 | 5 |
| Evaluated by the parent/guardian | 0      | 1 | 2 | 3 | 4 | 5 |

0 = medication administration failed; 1 = child is crying continuously; 2 = child is crying, screaming, or resisting, but not continuously; 3 = child shows some resistance to medication administration but does not cry or scream; 4 = good cooperation, but the child appears uncomfortable; 5 = good cooperation and calm breathing throughout medication administration. Adapted from Minh et al. [11]. If the nurse rates the medication administration as 0–2 points, the same dose is repeated once.

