## Study Implementation

### Study Design

This study is a randomized, investigator-blinded, multicenter clinical trial conducted in the pediatric emergency departments of Tampere, Oulu, and Kuopio University Hospitals, as well as at the Terveystalo outpatient clinic on [name] in Tampere, Finland. This is a pragmatic therapeutic clinical trial that does not involve blood sampling or any additional diagnostic procedures. Blinding is maintained for physicians involved in the emergency care inhalation therapy and research, for those entering data into the study database, and for the analysts evaluating the study results. The parents, child, and nurse are not blinded, as correct treatment administration requires the nurse to visually monitor the use of the spacer, including the fit of the mask and the movement of the valves in synchrony with breathing. The spacer devices being studied are approved for use in children both in Finland and internationally. The medication administered via the spacer follows the national evidence-based care guideline (Käypä Hoito) [8].

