### Study Procedure from the Patient's Perspective

#### Recruitment and Randomization

When a child aged 6 months to 4 years presents to the emergency department with acute bronchial obstruction, it is first confirmed that the child does not require immediate hospitalization and does not have any of the previously listed exclusion criteria. If eligible, the purpose of the study is explained to the parents, and they are given a patient information sheet to read (Appendix X, which they may keep).

While the parents review the form, the emergency nurse notifies the study unit's investigator, who confirms the diagnosis and the need for treatment. If the investigator is on call, they may personally enroll the child into the study. If the parents decide to participate, they are asked to sign an informed consent form (Appendix Y), of which a copy is also provided to them.

Randomization is conducted by biostatistician [name] (Oulu University Hospital), who is not involved in data collection. First, the spacer devices are coded as either Spacer A or Spacer B. Each center uses block randomization with randomly varying block sizes of 2, 4, or 6 (permuted blocks), as the study is single-blinded (blinding applies only to the study physician).

Randomization to the intervention or control group is carried out by assigning the first available study number between 001–00X to the child. Each participant has an equal probability of being allocated to either spacer group, as the assignment for each study number has been randomly pre-determined per center.

The assigned treatment group is sealed in an opaque envelope, which is opened in numerical order only after written consent has been obtained. The envelopes are prepared by a study nurse who does not participate in data collection. The group codes will not be unblinded until all study-related data has been recorded. Data analysis will be performed using the A and B group codes, meaning the investigators will not know which spacer corresponds to A or B until after the final analysis.

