### **Treatment of the Enrolled Child in the Emergency Department**

The study physician assesses the severity of the child's respiratory distress and records the RDAI score as well as other clinical variables listed in Table 3 on the study form. The child receives salbutamol via either the BH or OD spacer, with a dose based on weight (0.6 mg or 0.8 mg, corresponding to 6 or 8 actuations), up to four times at 20-minute intervals (Figure 4).

The study physician reassesses the clinical variables (Table 3) before treatment and again 20 minutes after the first two doses. If the child still requires bronchodilator treatment, up to two additional doses (0.6 or 0.8 mg, depending on weight) are administered. The physician again assesses breathing effort 20 minutes after the third and, if given, the fourth dose, and then makes the decision regarding further treatment (discharge or hospitalization, Figure 4). Otherwise, the follow-up and care of study participants will proceed in the outpatient clinic according to standard clinical practice.

In children under the age of 3, the spacer is used with a face mask; in older children, it may be used without a mask when appropriate. Salbutamol is administered one puff at a time into the spacer, and after each actuation, the child should take at least five breaths through the device. If the child strongly resists medication administration or is crying (Table 4), the same dose should be reattempted once the child has calmed down.

If a child enrolled in the Chamber study is discharged from the outpatient clinic, they will be given the spacer used during the study free of charge, along with written instructions for continued care. If the child is admitted to the hospital, treatment will continue on the ward using the same spacer device that was used in the emergency department.

**Figure 3.** Median dose of salbutamol delivered from spacer devices (% of nominal dose) and range measured using a filter (in vitro filter dose), when used without a mask (no mask) or with a mask (with mask). Measurements were performed using devices from three different production batches (LOT).

[figure not shown]

RR, respiratory rate. Vt, tidal volume.

LOT, production batch. P-values shown above the bars refer to differences with or without a mask, based on the Mann-Whitney U test.

P-values below the graph refer to differences between devices from different production batches, based on the Kruskal-Wallis test.

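### Oral corticosteroids given after randomisation are classed as a baseline characteristic; the item should be split by timing

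*Protocol*

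**What the plan says.** The entry on oral prednisolone in Table 3 of the protocol (Study Objectives) was amended on 25.2.2021, and the amended text is the rule in force. The need for the drug is struck out as a secondary outcome. In its place, the share of children given an oral corticosteroid "will be reported as baseline characteristic instead of outcome because they were often given before and/or during the intervention".

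Four other places bear on this rule:

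- **Recruitment and Randomization:** allocation envelopes are "opened in numerical order only after written consent has been obtained".
- **Study Objectives:** of the differences in delivered dose between the two spacers, the protocol says "These differences are assumed to affect the bronchodilator treatment response".
- **Study Design:** "Blinding is maintained for physicians involved in the emergency care inhalation therapy and research", whereas "The parents, child, and nurse are not blinded".
- **Sample Size:** the primary outcome is the final RDAI score, taken when the decision on discharge or admission is made.

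Care outside the inhalation schedule is left to standard practice (Summary; Treatment of the Enrolled Child in the Emergency Department). No section separates corticosteroids given before randomisation from those given after it.

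**The concern.** A baseline characteristic describes a child before allocation can have had any effect. By its own account, the amended entry includes treatment given after that point. The reason offered for the reclassification, that the drug was often given during the intervention, is the reason why the label fails for those children.

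Two things are at stake. First, the baseline table is where readers judge whether the arms were comparable at randomisation, and a line that mixes earlier and later use cannot serve that purpose. Second, corticosteroid use between randomisation and the final RDAI score is a co-treatment that readers need to see by arm when they interpret the RDAI result. If a child who responds poorly to the allocated spacer is more likely to be given a corticosteroid, part of any difference in use is a consequence of the device. Under a baseline heading it would be read as chance imbalance.

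**Working it through.** **Timing.** The order of events follows from the protocol:

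1. Consent is signed, then the envelope is opened (Recruitment and Randomization).
2. Salbutamol is given through the allocated spacer (Treatment of the Enrolled Child in the Emergency Department). The intervention cannot start before the allocation is known.
3. The final RDAI score is recorded at the outcome decision (Sample Size).

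A corticosteroid given during the intervention therefore falls between steps 1 and 3. It comes after randomisation and, in general, before the primary measurement.

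**Possible dependence on the device.** The protocol assumes that the devices differ in bronchodilator response. Physicians reassess the child during treatment, and other care follows standard practice. A blinded physician can still react to a weak response without knowing which spacer was used. Dependence on the device is therefore possible, but nothing in the protocol shows that it occurred.

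**What one pooled figure can and cannot show.** The protocol states no corticosteroid rate, so there is no figure of its own to reproduce. All rates below are assumed, with 40 children per arm (Sample Size). Count each child once, by whether the first corticosteroid came before or after randomisation. Then, for the difference between arms X and Y:

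pooled difference = difference before randomisation + difference after randomisation

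| Assumed case | Before, X v Y | Started after, X v Y | Pooled line, X v Y |
|---|---|---|---|
| A | 30% v 30% (12 v 12) | 25% v 10% (10 v 4) | 55% v 40% (22 v 16) |
| B | 45% v 30% (18 v 12) | 10% v 10% (4 v 4) | 55% v 40% (22 v 16) |
| C | 20% v 35% (8 v 14) | 35% v 20% (14 v 8) | 55% v 55% (22 v 22) |

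- Case A: 0 + 15 = 15 points, all after randomisation.
- Case B: 15 + 0 = 15 points, all before randomisation.
- Case C: −15 + 15 = 0 points. Two opposite differences cancel.

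A and B print the same line but mean different things, and C looks balanced although neither component is.

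**Precision of the split item.** 95% half-width for the difference in use started after randomisation = 1.96 × √[p₁(1−p₁)/40 + p₂(1−p₂)/40].

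- A: 1.96 × √(0.25×0.75/40 + 0.10×0.90/40) = 0.163, so 15 ± 16.3 points.
- B: 1.96 × √(2 × 0.10×0.90/40) = 0.131, so 0 ± 13.1 points.
- C: 1.96 × √(0.35×0.65/40 + 0.20×0.80/40) = 0.193, so 15 ± 19.3 points.

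At this sample size the split item is descriptive. It shows when the drug was given, but it would not settle a difference of 15 points.

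**The case against.** The strongest reply is that this is one descriptive line and that little depends on where it is printed. Several parts of that reply stand.

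- The amendment is partly sound. Corticosteroids given before randomisation are a proper baseline item, and their frequent use meant that need for prednisolone was not a clean outcome.
- A reader might infer that a difference between arms would be hidden. A baseline table by arm would still show the total; what is lost is its timing, and with it the meaning. Only where earlier and later use run in opposite directions, as in case C, would the total conceal a difference.
- A reader might infer that the device effect will be biased by adjustment for corticosteroids. The Statistical analysis section plans only unadjusted tests and names no covariate, so this is not a planned error.
- A reader might infer that treatment failure is no longer measured. Hospital admission and need for a fourth dose remain as secondary outcomes, so no formal outcome has to be reinstated.
- A reader might take the rule on additional doses in the emergency department as evidence that corticosteroids followed poor response. That rule concerns salbutamol only. Use during the intervention could equally be routine early treatment.
- Any effect of corticosteroids on the RDAI score comes from giving them and is the same whatever the label. No loss of power can be charged to this rule.

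It can also be said that table layout belongs in a statistical analysis plan. One may exist and may make the split. The protocol, however, does not leave the matter open: it assigns the whole item to baseline while stating that part of it came later. That is a wrong classification, not a missing detail.

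**Conclusion.** The point holds as a reporting error in the current text: corticosteroid use after randomisation is classed as baseline, and no other section corrects it. The conclusion rests on the protocol's own statement about timing and on the order of consent, allocation and treatment. It needs no assumed rate.

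The practical size is unknown. The protocol gives no corticosteroid rates and shows no difference between arms, and the three cases above only illustrate what a pooled line can conceal. Dependence on the device is plausible under the protocol's own assumption about response, but it is not demonstrated. The primary t-test and the retained outcomes are unchanged. What suffers is the validity of the baseline table and the reader's ability to see co-treatment before the primary measurement. The correction is worth making, but it is modest.

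**What to change.** Amend the Table 3 entry so that the item is split by time of administration relative to randomisation. Take the opening of the envelope as the dividing point, not the first inhaled dose.

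- Put only use before randomisation in the baseline table.
- Report use from randomisation to the final RDAI score by arm, as a post-randomisation co-treatment, with a risk difference and 95% CI. The Statistical analysis section already provides this format for proportions.
- Because the entry allows for use before and during the intervention in the same child, show children with both separately. Give unknown timing its own category.
- State that use after randomisation will not be treated as a baseline covariate if an adjusted analysis is ever added.

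This changes reporting only, not care. The cost should be small: administration times have to be retrieved from the charts at each site. The protocol does not say that these times are recorded on the study form, so some may be missing, and the unknown category then shows how many.

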## Study Implementation

### Study Design

This study is a randomized, investigator-blinded, multicenter clinical trial conducted in the pediatric emergency departments of Tampere, Oulu, and Kuopio University Hospitals, as well as at the Terveystalo outpatient clinic on [name] in Tampere, Finland. This is a pragmatic therapeutic clinical trial that does not involve blood sampling or any additional diagnostic procedures. Blinding is maintained for physicians involved in the emergency care inhalation therapy and research, for those entering data into the study database, and for the analysts evaluating the study results. The parents, child, and nurse are not blinded, as correct treatment administration requires the nurse to visually monitor the use of the spacer, including the fit of the mask and the movement of the valves in synchrony with breathing. The spacer devices being studied are approved for use in children both in Finland and internationally. The medication administered via the spacer follows the national evidence-based care guideline (Käypä Hoito) [8].

### Study Population

The study will include a total of 80 children aged 6 months to 4 years who are diagnosed with moderate or severe bronchial obstruction (RDAI score  $\geq 6$ , Table 2), and whose guardians have provided written, informed consent. The severity of respiratory distress is assessed using a previously published Respiratory Distress Assessment Instrument (RDAI) [12, 13].

Children will be excluded from the study at the emergency department if they meet any of the following criteria:

1. Require immediate inpatient care
2. Have an oxygen saturation ( $SpO_2$ ) below 85% upon arrival
3. Are diagnosed with bacterial or viral pneumonia
4. Show inspiratory crackles (suggestive of bronchiolitis in infants)
5. Are diagnosed with acute laryngitis (croup)
6. Are suspected to have or are confirmed to have a foreign body in the airway
7. Have liver or kidney dysfunction
8. Are immunocompromised or have another chronic condition deemed exclusionary by the attending physician
9. Have bronchopulmonary dysplasia due to prematurity
10. Are currently using a long-acting beta-agonist (LABA)
11. Have previously participated in this study
12. Refuse to take medication via spacer
13. Have participated in another clinical trial within the 30 days prior to enrollment

### Study Procedure from the Patient's Perspective

#### Recruitment and Randomization

When a child aged 6 months to 4 years presents to the emergency department with acute bronchial obstruction, it is first confirmed that the child does not require immediate hospitalization and does not have any of the previously listed exclusion criteria. If eligible, the purpose of the study is explained to the parents, and they are given a patient information sheet to read (Appendix X, which they may keep).

While the parents review the form, the emergency nurse notifies the study unit's investigator, who confirms the diagnosis and the need for treatment. If the investigator is on call, they may personally enroll the child into the study. If the parents decide to participate, they are asked to sign an informed consent form (Appendix Y), of which a copy is also provided to them.

Randomization is conducted by biostatistician [name] (Oulu University Hospital), who is not involved in data collection. First, the spacer devices are coded as either Spacer A or Spacer B. Each center uses block randomization with randomly varying block sizes of 2, 4, or 6 (permuted blocks), as the study is single-blinded (blinding applies only to the study physician).

Randomization to the intervention or control group is carried out by assigning the first available study number between 001–00X to the child. Each participant has an equal probability of being allocated to either spacer group, as the assignment for each study number has been randomly pre-determined per center.

The assigned treatment group is sealed in an opaque envelope, which is opened in numerical order only after written consent has been obtained. The envelopes are prepared by a study nurse who does not participate in data collection. The group codes will not be unblinded until all study-related data has been recorded. Data analysis will be performed using the A and B group codes, meaning the investigators will not know which spacer corresponds to A or B until after the final analysis.

### **Treatment of the Enrolled Child in the Emergency Department**

The study physician assesses the severity of the child's respiratory distress and records the RDAI score as well as other clinical variables listed in Table 3 on the study form. The child receives salbutamol via either the BH or OD spacer, with a dose based on weight (0.6 mg or 0.8 mg, corresponding to 6 or 8 actuations), up to four times at 20-minute intervals (Figure 4).

The study physician reassesses the clinical variables (Table 3) before treatment and again 20 minutes after the first two doses. If the child still requires bronchodilator treatment, up to two additional doses (0.6 or 0.8 mg, depending on weight) are administered. The physician again assesses breathing effort 20 minutes after the third and, if given, the fourth dose, and then makes the decision regarding further treatment (discharge or hospitalization, Figure 4). Otherwise, the follow-up and care of study participants will proceed in the outpatient clinic according to standard clinical practice.

In children under the age of 3, the spacer is used with a face mask; in older children, it may be used without a mask when appropriate. Salbutamol is administered one puff at a time into the spacer, and after each actuation, the child should take at least five breaths through the device. If the child strongly resists medication administration or is crying (Table 4), the same dose should be reattempted once the child has calmed down.

If a child enrolled in the Chamber study is discharged from the outpatient clinic, they will be given the spacer used during the study free of charge, along with written instructions for continued care. If the child is admitted to the hospital, treatment will continue on the ward using the same spacer device that was used in the emergency department.

**Figure 3.** Median dose of salbutamol delivered from spacer devices (% of nominal dose) and range measured using a filter (in vitro filter dose), when used without a mask (no mask) or with a mask (with mask). Measurements were performed using devices from three different production batches (LOT).

[figure not shown]

RR, respiratory rate. Vt, tidal volume.

LOT, production batch. P-values shown above the bars refer to differences with or without a mask, based on the Mann-Whitney U test.

P-values below the graph refer to differences between devices from different production batches, based on the Kruskal-Wallis test.

Figure 1. Study timeline in the emergency department

[figure not shown]

